**Demographic variables:**
*Age < 40 years versus > 40 years
*Higher education versus lower education
*Non-physical versus physically demanding jobs
**Anamnestic variables and neurological variables**
*Quetelet index < 25 versus > 25
*Influence of sitting on complaints versus no influence
*Straight leg raising < 30° versus low-back pain

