**Figure 1 F1:**
[figure not shown]
**Measuring the disk herniation**. The size of the herniated disc is measured in relation to the spinal canal diameter at disc level. The size should not exceed one third of the total spinal canal diameter.

**Table 1 T1:** Selection criteria for patient eligibility

Inclusion:
*Age 18–70 years
*Persistent Radicular pain lasting more than 6–8 weeks
*Operation indication
*Disc herniation confirmed at MRI
*Unilateral disc herniation smaller or equal to 1/3 of the spinal canal
*Informed consent
Exclusion:
*Previous surgery at the same disc level
*Cauda equina Syndrome
*Spondylolytic or degenerative spondylolisthesis
*Central spinal canal stenosis
*Pregnancy
*Severe somatic or psychiatric illness
*Planned (e)migration to another country in the year after the inclusion
*Inadequate verbal or writing skills in Dutch language

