### Sample size

The study is designed as an equivalence study with asymmetric boundaries, leading to a non-inferiority design. A difference of 4 on the Roland Disability Questionnaire has been recognized as the minimum clinically important difference. The power calculation is performed under the alternative hypothesis of a difference of 1 point on the Roland scale. By using this value 4 as the upper limit of the equivalence interval, with α-level of 0.05, a power of 0.90 and a SD of 5, the required sample size was 98 (49 per treatment arm). To adjust for an 8% loss to follow up, we plan to include 110 patients. These calculations are based on a comparison of average at single points in time. By using a repeated measurements analysis of variance, the power of the study over the entire follow-up period will be substantially higher (or equivalently, the average difference between the treatments can be established more accurately).

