### Statistical analysis

Baseline comparability between the two treatment groups will be evaluated with respect to disease characteristics, demographics and baseline values of self-report measures. Chi-square or Student t-test, as appropriate, will be used for these comparisons, although decisions to adjust for one or more of the base line characteristics in the actual analyses will not be based on statistical significance but on the relevance of the confounding effects in case of imbalance occurring in spite of the balanced randomization procedure. The analysis will be performed in accordance with the "intent-to-treat principle", analyzing all patients within their randomization groups, regardless of whether they completed the allocated treatment. Intent-to-treat analysis often leads to smaller observed treatment differences, thereby increasing the risk of type I error (claiming there is non-inferiority/equivalence, when there is not). Therefore, a per-protocol analysis is also carried out and differences in results will be described.

The analysis will consist of assessment of differences in outcome measurements between both groups and differences in time to recovery. It will take into account the stratification factors (center; research nurse) as covariates in accordance with ICH E9. Other base line covariates, measured before randomization, may be incorporated into the analysis models to increase power and to remove any residual confounding. An assessment of interaction between the treatment on the one hand and the stratification variables, or. main baseline covariates, will be considered as a mandatory part of the primary analysis and a proper interpretation of efficacy. The "difference" between the two treatment arms, the treatment effect (on the appropriate scale) will be reported both as an overall (adjusted) value and – in the case of significant effect modification – in terms of its dependence on the categories or values of the effect modifiers. A significant interaction between the stratifying factors or main baseline covariates will be considered as part of a proper modeling strategy and will not imply correction for repeated significance testing. After fitting the proper model, inference on the treatment effect will be based on the smallest fitting model that allows estimation of the treatment effect.

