When analyzing the primary outcome measure, Roland, the primary analysis will be a repeated measurement analysis of variance, hence estimating the original measurements. As a secondary analysis of this primary outcome variable, we will define "Roland-recovery" as a change of at least 11 points between baseline and any point in time post randomization. This dichotomization of the Roland score will be used as the outcome variable in a Cox regression analysis modeling time till recovery. The multivariate analysis will be performed along the same principles for variable selection and model building as outlined above.

A subgroup analysis is preplanned and will be performed to assess differences in treatment effect in subgroups of patients. (Table 4)

**Table 4 T4:** Prognostic variables in subgroup analysis

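### Table 4 examines age and Quetelet index as effect modifiers only through splits at 40 and 25, which leave patients exactly at a cut unassigned and usually cost information on the interaction

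*Protocol article*

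**What the plan says.** The Statistical analysis section states: "A subgroup analysis is preplanned and will be performed to assess differences in treatment effect in subgroups of patients". It points to Table 4, which gives age as "Age < 40 years versus > 40 years" and body mass index as "Quetelet index < 25 versus > 25". Table 4 gives no other form of either variable, and neither it nor the sentence that introduces it names a test.

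Earlier, the same section sets a separate requirement: "An assessment of interaction between the treatment on the one hand and the stratification variables, or. main baseline covariates, will be considered as a mandatory", within the primary analysis. Significant effect modification is to be reported "in terms of its dependence on the categories or values of the effect modifiers". That wording leaves room for a continuous modifier.

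Table 1 restricts entry to "Age 18–70 years". The Baseline data section records demographics, weight and length, so both variables can be used on their original scale.

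**The concern.** There are two separate problems.

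- **Gap at the cut.** With strict inequalities on both sides, age 40 and index 25 belong to no subgroup. Someone must place those patients later, possibly after outcomes are known.
- **Loss of information.** Asking whether the treatment effect differs between subgroups is a question of treatment-by-covariate interaction, whatever test is used. If the effect changes gradually with age or index, a split treats a patient of 41 like one of 69 and discards the gradient within each half.

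The Background section says that the subgroups are meant to identify patients who may particularly benefit from PLDD. The trial was sized for the overall comparison, so interaction assessments start out weak and the split weakens them further.

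**Working it through.** **Inputs from the Sample size section.** The margin is 4 points ("By using this value 4 as the upper limit of the equivalence interval"), the true difference is 1 ("under the alternative hypothesis of a difference of 1 point on the Roland scale"), the SD is 5, α is 0.05 and power is 0.90. The stated size is 98 (49 per arm), with 110 planned after an 8% allowance for loss.

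**The plan's own figure.** Taking α as one-sided, n per arm = 2·SD²·(z₀.₉₅ + z₀.₉₀)² / (4 − 1)² = 2·25·(1.645 + 1.282)² / 9 = 47.6, so 48. The noncentral t version gives 49 per arm, or 98, as stated. Allowing for loss, 98 / 0.92 = 106.5, so 107, close to the planned 110. N = 98 and SD = 5 are therefore sound inputs for the power check below.

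**Information kept by a split.** If the treatment effect is linear in X, the share kept is the squared correlation between X and the split indicator. For normal X cut c standard deviations from its mean, this is φ(c)² / [Φ(c)(1 − Φ(c))]. Signal-to-noise is multiplied by its square root.

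| c | groups | kept | lost | signal-to-noise factor | 98 patients act like |
|---|---|---|---|---|---|
| 0 | 50/50 | 0.637 | 36% | 0.80 | 62 |
| 0.5 | 69/31 | 0.581 | 42% | 0.76 | 57 |
| 1 | 84/16 | 0.439 | 56% | 0.66 | 43 |

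For a normal variable the median split is the best case, so 36% is the minimum loss.

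**Range over assumed distributions.** The article gives none, so these are assumptions.

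- Quetelet index, cut at 25, normal or lognormal, mean 24–28, SD 3–5: loss 36–61%.
- Age, cut at 40, normal truncated to the entry range, mean 38–48, SD 8–14: loss 32–56%. The low end comes from wide spreads centred near 40.
- Age uniform on 18–70: the share kept is 3p(1 − p) with p = 30/52, so 3 × 0.577 × 0.423 = 0.732, a loss of about 27%.
- Effect changing as a step exactly at the cut: no such loss, because the split is then the right form.

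**Effect on power.** Assume normal X, a linear modifier with slope b RDQ points per SD of X, N = 98, SD 5, two-sided 0.05 and a cut at the median.

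- Continuous term: SE = 2·5/√98 = 1.01.
- Split: the expected difference between halves is 1.596·b, with SE = 4·5/√98 = 2.02.
- b = 2: continuous 2/1.01 = 1.98, power 51%. Split 3.19/2.02 = 1.58, power 35%.
- b = 3: continuous 3/1.01 = 2.97, power 84%. Split 4.79/2.02 = 2.37, power 66%.

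**Patients at the cut, out of 110, under the same assumed distributions.** About 2 to 5.5 have a recorded age of 40 in whole years. For the index, about 1 has 25.0 if it is kept to one decimal, or 7–15 have 25 if it is rounded to whole units.

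**The case against.** The strongest reply is that these cuts govern less than they appear to. A reader might infer that the mandatory interaction assessment in the primary analysis will be run on the splits at 40 and 25. The article does not say so. That requirement names the stratification variables and main baseline covariates, does not refer to Table 4, and its reporting rule allows values as well as categories. The Background section presents the subgroups as a post-hoc analysis on factors defined in advance. This stands: the point is confined to the Table 4 analysis.

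A reader might also take it as fact that more than a third of the information is discarded. That needs a roughly normal covariate and a linear modifier. The 18–70 limits flatten the distribution of age, and the loss can then fall below a third. This also stands, and the figure has to be conditional.

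Further, cuts fixed in advance prevent a data-driven choice of threshold, readable groups suit the clinical aim, and a linear term can miss a threshold or a U shape. These are good reasons to keep the splits for display. They are not reasons to make them the only form in which the modifiers are assessed.

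Finally, the strict inequalities may be shorthand in a condensed table. That is likely, and few patients are probably affected. The text nevertheless leaves them unassigned, and the correction is trivial.

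**Conclusion.** The point holds as a minor one. The gap at the cut follows from the text without any assumption. The information loss is conditional: about 36% or more for a roughly normal covariate with linear modification. Under the assumed distributions it stays above a third for the Quetelet index, but runs from about 27% to 56% for age, and it does not arise if the effect steps at the cut. At the planned 98 evaluable patients, a median split could lower interaction power from about 51% to 35%, or from 84% to 66%, for slopes of 2 or 3 RDQ points per SD.

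It would go too far to conclude that the non-inferiority comparison is affected or the trial undersized. The sample size reproduces, and nothing in the primary comparison depends on Table 4.

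**What to change.** For the Table 4 analysis, state that treatment interaction with age and with Quetelet index is tested with each variable as a continuous linear term. Keep the prespecified splits for display, written as < 40 / ≥ 40 and < 25 / ≥ 25, so that every patient belongs to one group. Fix the wording before outcomes are examined by arm.

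The cost is a few words in the analysis plan, with no new data or patients, because the variables come from the baseline record. The downside is the linearity assumption: a linear term may miss a threshold or U-shaped effect, which the displayed splits would partly reveal.

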**MRI variables**
*Median versus mediolateral and lateral herniation
*High disc space versus low disc space
*Higher signal versus lower signal of disc on T2 weighted images
*Bud-herniation versus broad based herniation

Data will be stored via the internet-based secure data management system (ProMISe) of the department of Medical Statistics and Bioinformatics. The analysis will be carried out using SPSS.

## Discussion

With this publication we introduce the design of the first randomized controlled trial on the cost-effectiveness of PLDD versus conventional surgical discotomy for sciatica in lumbar disc herniation. This randomized controlled trial is a prospective trial comparing the effects of the techniques as well as the economical costs. The aim is to investigate whether both treatment modalities are equivalent in their clinical effect and to study their cost-effectiveness.

The inclusion is complete as off the end of 2007 with follow-up measurements going on until at least the end of 2009.

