**Discussion:**

Open discectomy is still considered to be the golden standard in the surgical treatment of lumbar disc herniation. Whether Percutaneous Laser Disc Decompression has at least as much efficacy as the standard surgical procedure, and is more cost-effective, will be determined by this trial.

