## Methods/Design

We designed a randomized prospective open trial aimed at showing non-inferiority of PLDD to the surgical treatment of lumbar disc herniation. Both treatments are compared in a parallel group design with at least a 2-year follow-up. The Roland Disability Questionnaire for Sciatica will be used as the primary outcome measure to determine the power of the study. A multi-center approach is used to assure a sufficient recruitment of participating patients. In this case 2 academic hospitals and 6 teaching hospitals will recruit patients. We received full approval of the ethics committees in all participating hospitals.

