### Outcome assessment

The assessment of outcome will use several validated outcome parameters as described below. Patients will undergo neurological examination by the research nurse at 4, 8, 26, and 52 weeks (Table 2). Questionnaires will also be filled out at these follow-up moments. At 1, 2, 6, 12, 38, 78, and 104 weeks the questionnaires will be filled out by the patient at home, and subsequently send to the data collection center by regular mail. Outpatient control by the neurosurgeon takes place at 8 weeks and thereafter if deemed necessary. The follow-up moments of data collection and outcome measures are listed in Table 3.

**Table 2 T2:** Neurological examination

*Straight leg raising test (Lasègue)
*Crossed straight leg raising test (Crossed Lasègue)
*Sensory loss
*Dermatome anesthesia
*Muscle weakness
*Knee tendon reflex difference
*Ankle tendon reflex difference
*Finger-ground distance in centimeter

Lasègue's sign is defined positive if the patient experiences a typically dermatomal area of pain reproduction and pelvic muscle resistance below a unilateral 60 degrees angle provocative straight leg raising. 'Crossed positive' if the same experience was noted with straight raising of the contralateral leg below 90 degrees.

**Table 3 T3:** Data collection and outcome measures

	RN			RN		RN		RN		RN		
**Time in weeks**	***X***	0	2	***4***	6	***8***	12	***26***	38	***52***	78	104

Treatment preference patient	v	v								v		v

Neurological examination	v			v		v		v		v		

Likert	v	v	v	v	v	v	v	v	v	v	v	v

Prolo	v			v		v		v		v		

Severity of complaints (VAS)	v	v	v	v	v	v	v	v	v	v	v	v

Functional status (Roland DQS)	v	v	v	v	v	v	v	v	v	v		v

McGill	v									v		v

Health status (Rand/SF 36)	v			v		v		v		v	v	v

EuroQol	v	v	v	v	v	v	v	v	v	v	v	v

SFB Index	v			v		v		V		v		

Costs (diary)	v		v	v		v	v	V	v	v		

Surgery/PLDD		v										

Complications		v		v		v		v		v		

"RN" marks the scheduled meetings with the Research Nurse.

Our goal is to show clinical equivalence between the two treatment strategies at various time points. The 1-year follow-up will be the most important clinical landmark. The cost-effectiveness analysis will therefore be performed using the clinical and economical parameters at 1 year.

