### Primary outcome measure

Roland Disability Questionnaire for Sciatica (RDQ) is an illness-specific 23-item functional assessment questionnaire that is frequently used for low back pain and sciatica [8-11]. The score, ranging from 0 to 23, reflect a sum of items experienced by the patient. The higher the score the more disabling the sciatica is perceived. The score will be analyzed as a continuous outcome variable. For descriptive purposes, "Recovery" (at the individual level) is defined by a difference of at least 11 points from baseline. A difference of 4 points for the averages between the two randomization arms is considered the maximum for "equivalence" of the two treatment modalities. The RDQ has established validity, reliability and responsiveness to change [12]. This outcome measure is used to determine the power of the study.

Other parameters that will be used from primary endpoint analyses are:

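### The primary hypothesis is worded in three ways (equivalence, non-inferiority, at least equal efficacy), but the design as sized supports only non-inferiority within 4 RDQ points

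*Protocol article*

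**What the plan says.** The protocol article gives the clinical objective in several places, and they do not agree.

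- **Equivalence.** Outcome assessment: "Our goal is to show clinical equivalence between the two treatment strategies at various time points". The closing Discussion: "The aim is to investigate whether both treatment modalities are equivalent in their clinical effect and to study their cost-effectiveness". Primary outcome measure defines the term without direction: "A difference of 4 points for the averages between the two randomization arms is considered the maximum for 'equivalence' of the two treatment modalities".
- **Non-inferiority.** Methods/Design, opening: "We designed a randomized prospective open trial aimed at showing non-inferiority of PLDD to the surgical treatment of lumbar disc herniation". The Background also hypothesises that the result is non-inferior at longer follow-up.
- **At least equal efficacy.** The abstract's Discussion says the trial will determine this: "Whether Percutaneous Laser Disc Decompression has at least as much efficacy as the standard surgical procedure".
- **Equivalence and non-inferiority together.** Sample size: "The study is designed as an equivalence study with asymmetric boundaries, leading to a non-inferiority design". Statistical analysis, describing the type I error, joins the two terms with a slash as if they were one conclusion.

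The calculation in Sample size names one limit: "By using this value 4 as the upper limit of the equivalence interval". No lower limit is stated anywhere in the article.

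**The concern.** Each of the three claims needs a different result. Let d be the mean RDQ difference, PLDD minus surgery, with positive values meaning PLDD is worse.

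- Non-inferiority needs d shown to be below +4.
- Equivalence, as Primary outcome measure defines it, needs d shown to lie between -4 and +4.
- At least equal efficacy needs d shown to be no greater than 0.

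A design with an upper limit alone delivers only the first. At stake is what may be concluded from a positive result. With the objective worded as it is, a reader of the final report could find support in the protocol for any of the three claims, although a passed test would have established one.

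**Working it through.** **Inputs (Sample size section).** Upper limit 4, assumed true difference 1, SD 5, α 0.05 (sidedness not stated), power 0.90, 98 patients (49 per arm).

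**1. Reproduce the stated sample size.** n per arm = 2(z₁₋α + z₁₋β)² SD² / (4 - d)².

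- One-sided 0.05: 2 × (1.645 + 1.282)² × 25 / 3² = 47.6, so 48 per arm. With the noncentral t distribution it is 49, exactly as stated.
- One-sided 0.025: 2 × (1.960 + 1.282)² × 25 / 3² = 58.4, so 59 per arm (60 with t). This does not match.

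So α is 0.05 on one side, which corresponds to a 90% confidence interval, and the 1-point difference is against PLDD (distance to the limit 4 - 1 = 3). The count alone does not show how many limits are tested, because step 3 needs the same n for two. That there is only one limit comes from the text: an upper limit, asymmetric boundaries, and a design called non-inferiority.

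**2. What a pass allows.** SE = 5 × √(2/49) = 1.010, and 1.645 × 1.010 = 1.66. The test passes when the observed d is below 4 - 1.66 = 2.34.

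- Take an observed d of 2.3. The 90% interval is 2.3 ± 1.66 = 0.64 to 3.96, which passes with every value on the worse side of zero. The 95% interval, 2.3 ± 1.98 = 0.32 to 4.28, also excludes zero.
- This happens for any observed d between 1.66 and 2.34. At the planning difference of 1, its probability is Φ((2.34 - 1)/1.010) - Φ((1.66 - 1)/1.010) = 0.907 - 0.744 = 0.16.
- If PLDD were truly 4 points better (d = -4), the one-sided test passes with probability above 0.999. A test against both -4 and +4 passes with probability 0.05.

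So a pass implies neither at least equal efficacy nor equivalence.

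**3. What the equivalence label would cost.** Take limits of ±4, each at one-sided 0.05, with 49 per arm. Power = Φ((4 - d)/SE - 1.645) + Φ((4 + d)/SE - 1.645) - 1.

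| True d | Non-inferiority | Within ±4 |
|---|---|---|
| +1 (planning) | 0.907 | 0.907 |
| 0 | 0.990 | 0.979 |
| -1 | 0.9995 | 0.907 |
| -2 (PLDD better) | 1.00 | 0.63 |
| -3 | 1.00 | 0.26 |

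At d = +1 the sum is 0.9074 + 0.9995 - 1 = 0.907. A simulation with t statistics gives 0.905 for both criteria. The smallest n for 90% power at d = +1 is 48 per arm by the normal approximation under either criterion. The ±4 criterion keeps at least 0.907 for true differences from -1 to +1 and loses power quickly once PLDD is better by more than that.

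**The case against.** The strongest reply is that the article settles its own terms. Sample size says openly that its form of equivalence leads to a non-inferiority design, and the Background and Methods/Design agree. On that reading *equivalence* is loose vocabulary for a declared one-sided test, and the abstract only poses a question. This stands in part: nothing is concealed and the operative hypothesis can be found. But Outcome assessment, Primary outcome measure and the closing Discussion use the word without that qualification, and no section reads the abstract's phrase as non-inferiority within 4 points.

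A second reply is that a condensed article may leave the decision rule to the full protocol or the SAP. That is fair, and no missing rule is criticised here. The objective itself is stated, in conflicting ways.

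Three stronger readings are tempting, and the document does not support them.

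- **That the cost-effectiveness analysis would treat the effects as equal and compare costs alone.** No section plans this. Outcome assessment says that analysis uses clinical and economic parameters at 1 year, and the Background expects a trade-off.
- **That a lower limit would protect against accepting a worse treatment.** A limit of -4 excludes only PLDD being better by 4 or more. It does nothing about a deficit. Nor does a true deficit of 4 points pass easily: the one-sided test lets it through about 5% of the time.
- **That equivalence could be had at no loss.** That is true at the planning difference, but not if PLDD is truly better by 2 points or more.

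**Conclusion.** The point holds as an inconsistency in the stated primary hypothesis. The design supports one conclusion, that PLDD is not worse than surgery by 4 or more RDQ points. A pass does not establish equivalence or at least equal efficacy. Under the protocol's own planning assumptions there is about a 16% chance of passing with a 90% interval wholly on the side unfavourable to PLDD. The sample size and the primary test need no change.

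This rests on three assumptions: α is one-sided 0.05 (the reading that reproduces 49 per arm), the 1-point planning difference is against PLDD, and any lower limit would be -4. The last is taken from the undirected 4-point definition in Primary outcome measure, since the article states no lower limit.

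**What to change.** 1. State one primary objective in the abstract, Background, Methods/Design, Outcome assessment, Primary outcome measure, Sample size, Statistical analysis and Discussion: PLDD is not worse than surgery by 4 or more RDQ points, judged by the upper limit of the two-sided 90% confidence interval for the difference.
2. Use *equivalent* only if the whole 90% interval lies within -4 to +4, and state the lower limit; otherwise drop the word. Keep this as a secondary label and not as a replacement for the primary test, because of the power loss when PLDD is better.
3. Reword the abstract's efficacy question as non-inferiority within 4 points.
4. In Statistical analysis, separate the two terms now joined by a slash.

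The cost is editing and one further limit read from an interval that is computed anyway. No patients are needed, and the article reports inclusion complete by the end of 2007. The price is a more modest headline claim. As the trial is open, the wording should be fixed and dated before outcomes are compared by arm.
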